### Plans to promote participant retention and complete follow-up {18b}

Aim 1/2: In-depth interviews: As these are one-time interviews, there is no retention plan.

Aim 2: Implement PPFP services in a clinic-randomized stepped-wedge trial: To increase attendance at PPFP follow-up appointments at one of the intervention facilities, we will reimburse women for their transportation/childcare costs for follow-up visits. To increase follow-up, we will also provide CHWs with lists of clients in their catchment areas who are pending follow-up to remind those women about their appointments.

Any identification of participation or follow-up rates that represent threats to our ability to sufficiently answer the research questions will be met with action by the PI to intervene to remedy the shortcomings.

### Data management {19}

PPFP logbooks will be maintained by trained PPFP providers in government facilities. Logbook data will be extracted into tablets weekly by the research field team through the mobile data collection platform Survey CTO v2.41 (Dobility, Cambridge, USA). Survey CTO data will be downloaded for weekly query and cleaning in a Microsoft Access database. Data will then be imported into SAS (Cary, NC) for analysis. A unique code will track clients from the community through ANC, L&D, and IV. This unique code is composed of personal information that the participant would remember (e.g., the first three letters of the mother’s name) but is unlinked to identifiers. We used this code in our previous pilot and were able to track > 95% of women who attended multiple visits at ANC, delivery/postpartum, and/or infant vaccination. For qualitative assessments, de-identified transcribed audio recordings will be stored on a secure server. Recruitment and missing data reports will be monitored weekly by the study coordinator, the PI, and the study statistician.

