## Methods: participants, interventions, and outcomes

### Study setting {9}

The Projet San Francisco (PSF)/Center for Family Health Research (CFHR) is an accredited non-profit organization established in Kigali, Rwanda, in 1986 and is committed to the pursuit of excellence in research and service delivery to improve family planning and LARC. PSF/CHFR will oversee all in-country implementation activities.

We will implement the PPFP intervention in 12 intervention facilities with high-volume labor and delivery (L&D) departments and will use our 5 pilot facilities as training sites in Kigali. These 17 facilities include 15 health centers (which provide antenatal care [ANC], family planning, and infant vaccination [IV] and refer L&D cases to adjoining hospitals) and 2 stand-alone hospitals (which provide routine L&D services and also receive referrals of high-risk and complex obstetric cases from health centers). The selected facilities are currently staffed with roughly 443 facility-affiliated CHWs, 35 ANC nurses, 188 L&D nurses/midwives, 41 family planning nurses, and 41 IV nurses. Additionally, over a 3-month period, these facilities serve roughly 4657 ANC clients, 4196 L&D clients, and 4371 IV clients. All facilities have the infrastructure for PPFP provision and procurement; though no formal PPFP initiatives are currently taking place, PP implant insertions are infrequent, and no providers are trained to insert PPIUDs. Our team has worked in these clinics (conducting clinic logbook data abstraction, implementing couples’ HIV counseling and testing, implementing interval LARC services, and surveying providers and patients) for over 10 years [6, 14–21].

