#### Reimbursements

Using the performance-based financing (PBF) system used by the Rwanda Ministry of Health as a guide [22], providers will be reimbursed for PPFP methods inserted, and these payments will be made to their facility and included in addition to their regular PBF pay. For context, providers receive PBF pay of US $0.60/new contraceptive method user regardless of method type, and the average salary for nurses working in family planning or L&D is US $124–364/month, depending on the educational level. CHW and Happy Clients will be reimbursed for their work.

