#### Effectiveness

Data on the number and proportion of clients receiving PPFP/PPLARC methods and experience of side effects will be abstracted from PPFP logbooks.

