**Clients delivering at implementation facilities**						
Promotions to pregnant or postpartum women/couples	268	17,870	2%	12,714	17,870	71%
PPIUD insertions	20	268	7%	3687	12,714	29%
PP implant insertions	14	268	5%	1399	12,714	10%

^a^Data from *n* = 12 government clinic logbooks, 2018

^b^Estimated from the pilot study [5]

^c^In ANC, L&D, FP, and IV

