## Data collection and management

### Plans for assessment and collection of outcomes {18a}

The number of stakeholders engaged and providers trained and certified will be recorded in an Advocacy and Training logbook. CHW counseling activities will be measured on referral slips which will record if a male partner was present. Women/couples receiving one-on-one PPFP counseling will have their method of interest, whether a male partner was present, household income, and estimated date of delivery recorded in a PPFP logbook, developed by the study team during the pilot and maintained by government clinic staff. The PPFP logbook will also record PPFP uptake and, among PP LARC users, provider perception of ease of insertion, client anxiety during insertion, and client pain during insertion (scales of 1–10). During follow-up visits, the PPFP logbook will record PPFP side effects and method failures. Facility information, client’s age, and parity will be abstracted from government Family Planning logbooks.

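### As written, LARC uptake is at risk of being recorded less completely in control than in intervention periods, because its only named source is a study logbook tied to counselling and trained providers

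*Protocol article*

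**What the plan says.** All references are to the Protocol article.

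- **Source of uptake.** Table 1 gives the PPFP logbook as the data source for the Effectiveness domain. The Effectiveness outcome text repeats it: "Data on the number and proportion of clients receiving PPFP/PPLARC methods and experience of side effects will be abstracted from PPFP logbooks". No second source for uptake is named.
- **Who is entered.** Under Plans for assessment and collection of outcomes {18a}: "Women/couples receiving one-on-one PPFP counseling will have their method of interest" and other items recorded in the logbook, which also records uptake. Government Family Planning logbooks are named there only for facility information, age and parity.
- **Who keeps it.** Section {18a} describes the logbook as "developed by the study team during the pilot and maintained by government clinic staff". Data management {19} says instead that "PPFP logbooks will be maintained by trained PPFP providers in government facilities".
- **The control condition.** Study setting {9}: "no formal PPFP initiatives are currently taking place, PP implant insertions are infrequent, and no providers are trained to insert PPIUDs". Table 5 lists 7 of 162 providers trained and 0 of 162 certified under control, against 78 and 70 under intervention.
- **Planning figures for control.** Footnote a of Table 5 gives their source as n = "12 government clinic logbooks, 2018", not the PPFP logbook.
- **Analysis.** Primary analyses {20a} assess uptake among women who delivered at a study facility. They compare intervention with control using a fixed effect for time and a random effect for clinic. There is no blinding {17a}.
- **Payment.** Under Reimbursements, "providers will be reimbursed for PPFP methods inserted"; the money goes to the facility, on top of regular performance-based pay.

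**The concern.** A stepped-wedge comparison is valid only if the outcome is recorded with the same completeness before and after crossover. Here the named recording instrument looks like part of the intervention. It was built for the pilot, it is filled in for women who have been counselled, and one section assigns it to staff whose training is itself an intervention component. The maintenance checklist for providers lists continued logbook use alongside PPFP trainings and promotions as a sign that the programme has taken hold.

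A woman in a control period who has an implant placed without study counselling could therefore count as a delivery with no LARC recorded. The same insertion after crossover is far more likely to be entered. The error pushes the primary comparison towards the intervention, and the cost-effectiveness comparison with standard of care inherits it.

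**Working it through.** **1. Table 5 reproduced.**
- PPIUD: 20/268 = 7.5% control, 3,687/12,714 = 29.0% intervention; odds ratio 5.06.
- PP implant: 14/268 = 5.2% control, 1,399/12,714 = 11.0% intervention (printed as 10%); odds ratio 2.24.

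These proportions use women who received promotions as the base. The primary analysis uses women who delivered, for whom Table 5 gives 17,870 per condition.

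**2. How much of each condition the logbook would cover.** I assume that Table 5's promotions approximate the women entered; Table 1 gives the PPFP logbook as the source for clients receiving PPFP information.
- Control: 268/17,870 = 1.5% entered, 98.5% outside.
- Intervention: 12,714/17,870 = 71.1% entered, 28.9% outside.

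This gap does not depend on who holds the pen. It remains if the keepers are government clinic staff, who are present in both periods. If the keepers are trained providers, 7/162 = 4% are available under control against 78/162 = 48%, which widens it.

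**3. What that does to the contrast.** Suppose uncounselled women in both conditions take up LARC at the same rate u and none of it is recorded. Unrecorded uptake is then 0.985u under control and 0.289u under intervention. The risk difference is overstated by

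u × (12,714 − 268)/17,870 = 0.696u.

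For assumed u of 0.5%, 1% and 2% this is 0.35, 0.70 and 1.4 percentage points. The documents do not give u.

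**4. Effect on the planned odds ratio when there is no true effect.** Let true uptake be p in both conditions, with full capture after crossover and capture c under control. The recorded odds ratio is (1 − cp)/[c(1 − p)].
- p = 0.11, c = 0.9: 0.901/0.801 = 1.12.
- p = 0.11, c = 0.8: 0.912/0.712 = 1.28.
- p = 0.29, c = 0.9: 0.739/0.639 = 1.16.
- p = 0.29, c = 0.8: 0.768/0.568 = 1.35.

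Take 8,935 women per condition (17,870 split evenly), a two-sided alpha of 0.05, and ignore clustering. With p = 0.11, a two-proportion test would then reject in 67% of trials at c = 0.9 and 99.8% at c = 0.8. Clustering would lower these rates but not the bias. The values of c, the alpha and the even split are assumptions; the article states alpha only for the safety interim analysis.

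**5. Can the model absorb it?** The stated model contains the intervention indicator, period effects common to all clinics, and a clinic effect constant over time. If capture in a clinic rises when that clinic crosses over, it varies with exactly the same clinic-by-period pattern as the intervention indicator. The intervention coefficient then carries true effect and recording change together, and neither of the other terms can separate them.

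**The case against.** The strongest reply is that differential recording is inferred, not stated. No sentence says that the logbook is absent in control periods. Table 2 has effectiveness data collected throughout the stepped-wedge implementation, the keepers are elsewhere given as ordinary clinic staff, and transfers between intervention and control facilities will be recorded. The detail may sit in the full protocol or operating procedures. This stands as far as it goes: the point is a risk in the plan as written, not a demonstrated fault. It does not dispose of the point, because the article positively names one uptake source and describes entry by counselling. That is a choice made, not a detail left out.

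Three stronger readings are tempting and are not supported.

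- **That recorders exist only after crossover.** Table 5 has 7 of 162 providers already trained under control, and {18a} names government clinic staff.
- **That hundreds of control implants would be lost.** A reader might take the pilot's 178% increase (ratio 2.78), compute 1,399/2.78 = 503 control implants, 36 times the 14 in Table 5, and contrast an odds ratio of 108 with about 3 by putting the counts over 17,870. The ratio comes from five non-randomised pilot facilities and a before-after comparison. The 14 implants already come from government logbooks, so they cannot show what a PPFP logbook misses. Table 5's own bases give 2.24, not 108.
- **That payment inflates intervention entries.** Payment goes to the facility, a US $0.60 payment per new user already exists outside the study, and the start of the added payment is not stated. Logbook data are also extracted weekly and queried. Over-recording is at most a secondary possibility.

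**Conclusion.** The point holds as a risk of differential ascertainment in the primary comparison, running in favour of the intervention. It rests on three things the article states: a single uptake source, entry through one-to-one counselling, and an analysis base of all deliveries. Together with Table 5's expected reach of 1.5% against 71%, these would leave most control deliveries outside the recording frame if the plan were followed literally.

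The size of the bias cannot be derived, because neither control-period capture nor uptake among uncounselled women is given. The figures in steps 3 and 4 show only that modest under-capture is enough to matter for an odds ratio. Which method is more exposed is also unclear: the setting section suggests almost no control PPIUDs, yet Table 5 lists 20 of them against 14 implants. The source should be settled before uptake data are abstracted, since the planned model cannot correct it afterwards.

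**What to change.** - State one source for LARC uptake and for the delivery denominator, used in all 12 clinics and in every control and intervention period: the government family planning and delivery registers. The research team should abstract them with the same form and one stated postpartum window, for example the 14 weeks already used in the eligibility criteria.
- Keep the PPFP logbook for counselling, promotion and process data.
- Reconcile {18a} with {19} on who maintains the logbook, and reconcile the statement that "no providers are trained to insert PPIUDs" with the 20 control PPIUD insertions in Table 5.
- Checking recorded insertions against device stock is optional.

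The cost is modest: additional register abstraction by a field team that already extracts logbook data weekly and is due to abstract government Family Planning logbooks. No new procedure falls on women. The team should first confirm that the registers distinguish postpartum from interval insertions. The 2018 control counts of PPIUDs and PP implants suggest they can, but the article does not say so.

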### Confidentiality {27}

We will minimize the risk of any loss of confidentiality throughout the study design and conduct. These features will be included in standard operating procedures (SOPs) as follows:
All study procedures will be conducted in private, to the extent possible.A trained research staff member will administer all in-depth interviews and mixed-methods surveys conducted in specific aims 1 and 3, respectively.Individual subjects will not be identified by the data collected; it will be used for research purposes only and no personal identifiers will be used.All non-electronic research-related information will be securely stored in locked file cabinets in locked rooms with restricted access at PSF/CFHR.All electronic records will be kept in password-protected files. All electronic communications of study data will be through password-protected, encrypted files. All data storage at Emory University or PSF/CFHR will be on firewall-protected servers.All staff participating in data collection or management have been/will be certified in Good Clinical Practices (GCP) and will attend documented trainings regarding the protection of human subjects.Per the Data and Safety Monitoring Plan, data and data collection and management procedures will be reviewed at least annually.Informed consent documents will describe confidentiality and the legal limits of confidentiality.

No identifiable protected health information will be collected under this protocol. All data will be entered into a password-secured access database. Any non-electronic research-related information will be stored in locked file cabinets in locked rooms with restricted access.

### Plans for collection, laboratory evaluation, and storage of biological specimens for genetic or molecular analysis in this trial/future use {33}

This trial does not involve collecting biological specimens (please see Additional consent provisions for collection and use of participant data and biological specimens {26b}).

## Statistical methods

### Statistical methods for primary and secondary outcomes {20a}

#### Reach and adoption

We will tabulate, overall and by facility, the number of stakeholders engaged, providers trained, promoters trained, providers certified and pre/post-training evaluation scores, and clients who received one-on-one counseling. We hypothesize increases comparing intervention versus standard of care in stakeholders engaged, providers trained to promote and provide PPFP, and couples/clients receiving information about PPFP (Table 5). We expect 90% of trainees will receive certification to promote and provide PPFP.

#### Effectiveness

##### Primary analyses

We will tabulate, by facility, a total number of all PPFP methods provided and the proportion of PPFP uptake among women who delivered at one of our facilities (overall and by method type). PP LARC uptake (by method type) will be evaluated using logistic regression and general estimating equation methods to account for the clinic-randomized design. The main predictor will be the intervention versus the control arm. For example, the following generalized linear mixed model will compute the adjusted odds ratio for taking up a PP implant: *Y*_*ijl*_ = *β*0 + *β*1 × (intervention_*ij*_) + *β*2 × (covariates_*ij*_) + *β*3 × (intervention_*ij*_ × covariates_*ij*_) + *β4*_*j*_ + *u*_*i*_ + *ε*, where *i* = clusters*, j* = time periods, *l* = individuals, *β*1 = fixed effect for intervention, *β*2 = fixed effects for covariates, *β*3 = fixed effects for interactions, *β*4_*j*_ = fixed effect for time, *u*_*i*_ = random effect for ICC, and *ε*_*ijl*_ = random residual. Covariates assessed as potential confounders will include facility volume, service volume-to-staffing ratio, and number of promotions received. Outcomes will be reported as adjusted odds ratios with 95% confidence intervals. We hypothesize that the intervention will significantly increase PP LARC uptake by comparing intervention versus control. We will also assess the independent effect of each promotional strategy on PP LARC uptake. Every promotion will be recorded and we will estimate the independent effect of receiving CHW counseling, video-based promotions, or Happy Client promotions (treating each strategy as an independent, dichotomous exposure of interest) on PPFP uptake using adjusted multivariate regression modeling with general estimating equations methods.

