**Methods:**

In a type 2 effectiveness-implementation hybrid study, we will evaluate the impact of our PPFP intervention on postpartum LARC (PPLARC) uptake in a clinic-randomized trial in 12 high-volume health facilities in Kigali, Rwanda. We will evaluate this hybrid study using the RE-AIM framework. The independent effectiveness of each PPFP demand creation strategy on PPLARC uptake among antenatal clinic attendees who later deliver in a study facility will be estimated. To assess sustainability, we will assess the intervention adoption, implementation, and maintenance. Finally, we will evaluate intervention cost-effectiveness and develop a national costed implementation plan.

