### Objectives {7}

Aim 1: Implement the intervention in 12 high-volume health facilities: Guided by the Consolidated Framework for Implementation Research [9, 10], we will engage stakeholders and assess facility organizational readiness prior to implementation. No PPFP activities are currently taking place in these facilities. We will implement the PPFP intervention in a clinic-randomized stepped-wedge design. We expect to deliver PPFP promotional counseling to over 21,000 pregnant or postpartum women/couples.

Aim 2: Evaluate intervention effectiveness and implementation: The RE-AIM framework [11] will guide the outcome evaluation. We hypothesize that the intervention will significantly increase the number of stakeholders engaged, PPFP providers and promoters, couples/clients receiving information about PPFP, and LARC uptake comparing intervention versus standard of care. We expect PPFP client satisfaction will be high, and side effects will be rare. The independent effectiveness of each demand creation strategy on LARC uptake will be estimated. We assess the measures of intervention adoption, implementation, and maintenance at the patient, provider, and stakeholder levels to assess the intervention sustainability.

Aim 3: Evaluate intervention cost-effectiveness and cost-utility: We employ standard methods [12, 13] to estimate the costs and incremental cost-effectiveness and cost-utility of the intervention relative to the standard of care from the societal perspective. The cost-effectiveness of each demand creation strategy will be estimated. We hypothesize that the intervention will be cost-saving relative to the standard of care. A costed implementation plan will be developed to guide Rwandan MOH decision-making for the nationwide roll-out of PPFP services.

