### Outcomes {12}

RE-AIM will guide outcome assessment (Table 1).

**Table 1 Tab1:** RE-AIM domains and measures

Domains	Outcome measures	Data source
**Reach**	^a^Stakeholders engaged and PPFP providers/promoters trained	Advocacy and training study log
	^a^Couples/clients receiving information about PPFP	PPFP logbook
**Effectiveness**	^a^Clients receiving PPFP/PP LARC methods PPFP side effects	PPFP logbook
**Adoption**	^a^Providers/promoters providing PPFP	Advocacy and training study log
**Implementation**	Provider/promoter time to provide PPFP Patient wait times to receive PPFP Implementation fidelity	Time motion studies, fidelity checklist
**Maintenance**	Woman/couple-level: continued PPFP use at 9 months, factors associated with PPFP uptake and continued use	Interviews, PPFP logbook
	Provider/facility-level: progress toward institutionalizing PPFP, factors associated with PPFP continued provision at the end of implementation	Interviews, standardized checklist
	Stakeholder-level: progress of the Ministry of Health to nationalize PPFP services at the end of implementation	Interviews

^a^Quantitative outcomes used in power analyses, see Table 5

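### The article names more than one effectiveness outcome: the promotional-strategy model switches from PPLARC to any PPFP method, and no stated model directly tests the hypothesis for PPLARC as a whole

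*Protocol article*

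**What the plan says.** **Overall effect.** The abstract (Methods) poses one question: "we will evaluate the impact of our PPFP intervention on postpartum LARC (PPLARC) uptake in a clinic-randomized trial". Aim 2 in Objectives {7} and the hypothesis in Statistical methods {20a}, Effectiveness, Primary analyses are likewise about LARC uptake without a split. The Background describes LARC as including the copper IUD and the implant. The regression sentence, however, reads: "PP LARC uptake (by method type) will be evaluated using logistic regression and general estimating equation methods". The model written out as an example is for the implant. Table 5 in Sample size {14} has a PPIUD row and an implant row, and none for the two together.

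**Promotional strategies.** The abstract states the outcome and the population: "The independent effectiveness of each PPFP demand creation strategy on PPLARC uptake among antenatal clinic attendees", continuing to those who later deliver in a study facility. Objectives {7} agrees on the outcome: "The independent effectiveness of each demand creation strategy on LARC uptake will be estimated". The primary-analysis text begins in the same way: "We will also assess the independent effect of each promotional strategy on PP LARC uptake". The next sentence says the effect of CHW counselling, video or Happy Client promotion will be estimated "on PPFP uptake using adjusted multivariate regression modeling with general estimating equations methods".

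**Outcome table.** Table 1 in Outcomes {12} gives the effectiveness measure as "Clients receiving PPFP/PP LARC methods", naming both outcomes with a slash and not ranking them.

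**The concern.** PPFP and PPLARC are different outcomes. The section on PPFP service delivery training lists injectables and pills among PPFP options, and Adverse event reporting and harms {22} also covers tubal ligation. A strategy that raised only pill or injectable use would count as effective in the model as written, although the abstract and Aim 2 ask about LARC. The population matters too. Eligibility {10} extends to women up to 14 weeks postpartum, so leaving out the antenatal restriction lets in women whose first contact came after delivery.

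For the overall effect, two device-specific odds ratios do not add up to a test of the stated hypothesis. The two devices are alternatives for most purposes, so each result depends partly on what happens with the other device. The article does not say how the two results together would confirm or refute an increase in PPLARC uptake.

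**Working it through.** **Step 1: the texts side by side.**

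| Place | Question | Outcome named | Population named |
|---|---|---|---|
| Abstract, Methods | Overall effect | PPLARC | Not stated |
| Objectives {7}, Aim 2 | Overall effect | LARC | Not stated |
| Primary analyses, hypothesis | Overall effect | PP LARC, unsplit | Not stated |
| Primary analyses, regression | Overall effect | PP LARC by method type; example is the implant | Not stated |
| Table 5 | Overall effect | PPIUD and implant rows | Women receiving promotions |
| Abstract, Methods | Strategies | PPLARC | Antenatal attendees who later deliver in a study facility |
| Objectives {7}, Aim 2 | Strategies | LARC | Not stated |
| Primary analyses, first strategy sentence | Strategies | PP LARC | Not stated |
| Primary analyses, next sentence | Strategies | PPFP | Not stated |

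The paragraph does specify reporting both overall and by method type, but only for the descriptive tabulation of PPFP uptake among women who delivered at a study facility. The regression sentence has the method-type part alone.

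**Step 2: the plan's own figures.** Inputs from Table 5: PPIUD 20/268 and 3687/12,714; implant 14/268 and 1399/12,714.
- PPIUD: 7.5% versus 29.0%.
- Implant: 5.2% versus 11.0% (the intervention figure is printed as 10%).
- The plan claims more than 80% power for every row. With no allowance for clustering, and assuming a two-sided alpha of 0.05, power is about 100% for PPIUD and 92.7% for the implant (84.7% with the printed 5% versus 10%). The clustered claim cannot be reproduced because the article gives no ICC value. In any case it covers the two device rows and not the combined outcome.

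**Step 3: the combined outcome.** Assume each woman takes one device.
- Control: (20 + 14)/268 = 34/268 = 12.7%.
- Intervention: (3687 + 1399)/12,714 = 5086/12,714 = 40.0%.
- Odds ratio: (5086/7628)/(34/234) = 0.6668/0.1453 = 4.59.

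**Step 4: the device-specific contrasts.**
- PPIUD: (3687/9027)/(20/248) = 5.06.
- Implant, PPIUD users counted as non-users: (1399/11,315)/(14/254) = 0.1236/0.0551 = 2.24.
- Implant, PPIUD users removed: (1399/7628)/(14/234) = 3.07.
- PPIUD users' share of implant non-users under the first coding: 3687/11,315 = 32.6% with intervention, 20/254 = 7.9% in control.

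Neither implant figure equals the any-LARC figure, and the choice between them depends on coding that the article does not give. The denominators here are women receiving promotions, so these are illustrations and not forecasts of the trial result.

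**The case against.** **PPFP is itself a listed outcome.** Table 1 names PPFP beside PP LARC as an effectiveness measure, so modelling PPFP uptake is not out of place. That stands, and it is a reason to keep any-PPFP uptake as a secondary outcome. It does not reconcile two consecutive sentences that name different outcomes for the same strategy analysis.

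**Analysis by device is legitimate.** Table 5 and the pilot results are given by device, and the devices start from different supply positions: implants are inserted infrequently, and no provider is trained to insert PPIUDs. This stands. The device results should be reported; the gap is the absence of a stated model for the overall hypothesis.

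**The regression sentence may mean PP LARC overall with a breakdown, and an unseen analysis plan may say so.** This is possible. A reader might infer that combined uptake will never be analysed, but the text does not go that far. It shows only that no such model is stated here. An analysis plan could add the model; it could not make both strategy sentences correct.

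**Coding is not given.** A reader might take it as settled that a PPIUD user counts as a failure in the implant model. That is the ordinary reading of a binary model, but it remains an inference.

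**Substitution could make the implant look harmful.** If implant choice among women without a PPIUD stayed at 14/248 while PPIUD uptake rose to 29%, implant uptake would be 0.71 × 5.65% = 4.0% against 5.2%, an odds ratio of about 0.76. The documents do not support expecting this: Table 5 projects more implants, and in the pilot both devices rose.

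**The denominator changes the size.** On the 17,870 delivering clients in each column of Table 5, the implant odds ratio is (1399/16,471)/(14/17,856), about 108, which would not look weak. So the 2.2 is specific to promotion recipients.

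**Conclusion.** The concern holds in two parts. First, the strategy analysis contradicts itself on its outcome, departs from the abstract and Aim 2, and omits the abstract's population. This rests on the text alone. Second, the hypothesis for PPLARC as a whole has no explicitly stated model and no row in Table 5. This also rests on the text, with the reservation that the regression sentence is somewhat ambiguous.

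The size is illustrative: an any-LARC odds ratio of about 4.6, against about 2.2 for the implant under ordinary binary coding. This assumes one device per woman, Table 5's promotion-recipient denominators and no adjustment for clustering or time. Under those assumptions the implant result understates the any-LARC effect. It is not evidence that the implant analysis would show harm.

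**What to change.** 1. In the strategy sentence of Primary analyses, make PPLARC uptake the modelled outcome, among antenatal attendees who later deliver in a study facility, as in the abstract. Keep any-PPFP uptake as a secondary outcome.
2. State one binary outcome per woman, any PPLARC (PPIUD or implant), as the outcome of the primary intervention-versus-control model. Report the PPIUD and implant models beside it as secondary, and say how users of the other device are coded in each.
3. Add a combined row to Table 5: about 34/268 (12.7%) versus 5086/12,714 (40.0%), if each woman takes one device.

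The cost is wording in Primary analyses and Sample size {14}, plus one variable derived from uptake already recorded in the PPFP logbook. On Table 5's counts the change does not lose power. With an assumed design effect of 10 applied to both arms and a two-sided alpha of 0.05, power is 90.5% for any PPLARC, 79.2% for PPIUD and 8.1% for the implant. At a design effect of 2 the figures are about 100%, about 100% and 59.1%. The downside is that the device-specific results become secondary.
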